## Abstract

**Background:**

Major depressive disorder is among the most disabling illnesses worldwide, with a lifetime prevalence of 16.2%. Research suggests that 20% to 40% of patients with depression do not respond to pharmacotherapy, developing treatment-resistant depression. Electroconvulsive therapy is the gold standard for treating individuals with treatment-resistant depression, with remission rates of approximately 75% to 90%. However, 10% to 25% of patients do not respond to electroconvulsive therapy, and many are unable to tolerate it due to the side effects. Both groups are considered to be patients who do not respond to electroconvulsive therapy, because both groups continue to exhibit symptoms of severe depression, have a limited number of treatment options available, and are in need of rapid treatment. Ketamine, an N-methyl-D-aspartate receptor antagonist, has been shown to exert rapid antidepressant effects in patients with treatment-resistant depression when administered in subanesthetic doses through 40-minute intravenous infusions. Recently, a ketamine compound, esketamine (Spravato), that is administered through the intranasal route received regulatory approval by the US Food and Drug Administration and Health Canada to treat depression. However, esketamine is challenging to access due to high costs and limited availability. Racemic ketamine (rketamine) is cheap and easy to access; however, the effects in patients who have not responded to electroconvulsive therapy have yet to be understood or tested. This study will use transcranial magnetic stimulation to study mechanisms of human brain cortical physiology at the systemic level to identify neurobiomarkers of response.

**Objective:**

The objective of this open-label pilot clinical trial is to test the feasibility and safety of intranasal ketamine in patients who have not responded to electroconvulsive therapy. The primary outcome is to determine the feasibility of a larger randomized controlled trial to test the efficacy of intranasal ketamine for patients who have not responded to electroconvulsive therapy for clinical indicators in unipolar depression. The secondary outcome is to determine the preliminary effects of an intervention on clinical outcomes, such as depressive symptoms, suicidal ideation, and quality of living. The third outcome is to explore neurophysiological changes as measured by transcranial magnetic stimulation electromyography and electroencephalography to measure changes in cortical excitability as potential predictors of clinical response.

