**Conclusions:**

This is the first study to test repeated doses of intranasal rketamine in patients who have not responded to electroconvulsive therapy for depression. Results from this study will (1) inform the development of a larger adequately powered randomized controlled trial to test the efficacy of intranasal ketamine for depression and (2) determine potential neurophysiological markers of clinical response.

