### Statistical Analysis

#### Statistical and Analytical Plans

Baseline participant characteristics will be reported and described using summary statistics—mean and standard deviation for continuous data and number and proportion for categorical data. The primary analysis to determine if there is a statistically significant effect of intranasal ketamine on depressive symptoms will be the paired 1-tailed *t* test of the HDRS-24 score at baseline to week 4. We will also report the standardized mean difference as a measure of effect size (small: 0.2; medium: 0.5; large: 0.8 [40]). For tolerability and safety outcomes, we will report the number and proportion of individuals who experience a transient increase in blood pressure, agitation, and behavioral disturbance. To assess suicidality change, we will use the 1-tailed paired *t* test from baseline to week 4 of the Scale of Suicide Ideation score and calculate the standardized mean difference. For neurophysiology, we will use the 1-tailed independent *t* test to compare components of TMS-evoked responses at left dorsolateral prefrontal cortex. In addition, we will use the nonparametric cluster-based permutation test to investigate any significant changes in overall EEG channels.

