## Discussion

To our knowledge, this is the first study to test repeated doses of rketamine delivered intranasally in patients with major depressive disorder who did not respond (either clinically or due to their inability to tolerate) to an acute course of electroconvulsive therapy. The use of neurophysiological tools to assess changes in cortical excitability will provide preliminary data for potential biomarkers of response, which can be further assessed in a larger clinical trial. A lack of control group and small sample size are limitations of the current protocol. However, given that it is a pilot open-label clinical trial, the sample size is sufficient (ie, the goal is not to assess generalizability or statistical significance). The lack of blinding in the control group is a common concern in ketamine trials [27], because a placebo with comparable effects does not exist, and it is impossible to ensure blinding to the full extent. Because the study is being conducted at a single site of a large psychiatric academic facility, the results may not be transferable to a broader population.

Results will be presented during scientific conferences, in clinical rounds, and publications in relevant journals.

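### The stated neurophysiology analyses are not explicitly linked to HRSD-24, although the protocol promises potential predictors and markers of clinical response

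*Protocol article*

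**What the plan says.** The abstract's Objective gives the third outcome as exploring neurophysiological change by TMS with electromyography and electroencephalography, "to measure changes in cortical excitability as potential predictors of clinical response". The abstract's Conclusions list two things the results will do. One is to inform a larger trial; the other is to "determine potential neurophysiological markers of clinical response". The Background and the Introduction make similar claims. The Discussion is more guarded: the measurements "will provide preliminary data for potential biomarkers of response, which can be further assessed in a larger clinical trial".

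Statistical and Analytical Plans states two neurophysiology analyses. The first is "we will use the 1-tailed independent *t* test to compare components of TMS-evoked responses at left dorsolateral prefrontal cortex". The second is a "nonparametric cluster-based permutation test to investigate any significant changes in overall EEG channels".

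The same section analyses depression separately, by a paired 1-tailed "test of the HDRS-24 score at baseline to week 4". It mentions no correlation, regression or subgroup comparison that brings the neurophysiological and clinical data together. The article defines non-response to electroconvulsive therapy for eligibility, but it gives no definition of response to ketamine.

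**The concern.** Whether a signal changes under treatment and whether it tells us who gets better are different questions. A TMS-evoked component that moved by the same amount in all 25 patients would give a highly significant change and no information about response. There is no control arm ("A lack of control group and small sample size are limitations of the current protocol"), so such a shift could not be separated from time or repeat testing either.

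Followed as written, the plan leaves the second deliverable without a clearly stated supporting result. Two consequences are possible. A general drug or time effect on the EEG could be reported as a biomarker of response. Or the link to response could be sought after the data are seen, across many components and 64 channels, with nothing fixed in advance.

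**Working it through.** **Promise and plan side by side**

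| Stated aim or analysis | Question it answers | Uses HRSD-24? |
|---|---|---|
| Third outcome; abstract Conclusions | Does neurophysiology predict or mark response? | It has to |
| Cluster-based permutation test | Does the EEG signal change? | No |
| 1-tailed independent t test of evoked components | Unclear, because no groups or time points are named | Not stated |
| Paired t test of HRSD-24 | Does depression improve? | Yes, but no neurophysiology |

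No row explicitly joins the two kinds of data. The t test has two plausible readings.

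**Reading A: baseline against post-treatment.** The same patients supply both sets of values, so the independent test uses the wrong standard error. With common standard deviation s and pre-post correlation ρ:

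- independent formula: SE = s√(2/n)
- paired: SE = s√(2(1−ρ)/n)
- ratio: 1/√(1−ρ)

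At ρ = 0.5 the ratio is 1/√0.5 = 1.41. At ρ = 0.9 it is 1/√0.1 = 3.16. Both correlations are assumptions. The Study Measurements section reports test–retest reliability above 0.9, but the correlation across a treatment course could be lower. On this reading the independent test overstates the standard error, and the result still says nothing about response.

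**Reading B: responders against non-responders.** This does bear on response, but the groups cannot be formed from the article because no cut-off is given. Inputs: n = 25 (protocol); difference d = 0.8 SD, a 12/13 split and alpha 0.05 (all assumed).

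- noncentrality = 0.8/√(1/12 + 1/13) = 0.8/0.4003 = 2.00, with 23 degrees of freedom
- two-sided critical value 2.069: power 0.48
- one-sided critical value 1.714, matching the plan's single tail: power 0.62

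An assumed 5/20 split lowers these: noncentrality 0.8/√(1/5 + 1/20) = 1.60, with power 0.34 two-sided and 0.46 one-sided. For 80% power, the difference would have to be 1.03 SD one-sided or 1.17 SD two-sided at 12/13, and 1.28 or 1.46 SD at 5/20.

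**Precision of a direct estimate.** Fisher's z for an assumed correlation of 0.4 at n = 25:

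- atanh(0.4) = 0.424; SE = 1/√22 = 0.213; half-width = 1.96 × 0.213 = 0.418
- limits on the z scale: 0.006 and 0.842
- back-transformed 95% interval: 0.006 to 0.687, about 0.01 to 0.69

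For an assumed correlation of 0.3 the interval is −0.11 to 0.62. The smallest correlation detectable with 80% power at n = 25 is tanh((z_alpha + z_power)/√22): 0.49 one-sided or 0.53 two-sided. If only 20 patients had usable data (assumed), these become 0.54 and 0.59.

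The protocol has no figure of its own to reproduce here. Its 25 is an accrual estimate (250 × 0.25 × 0.20 × 2 = 25) and has no bearing on an association with response.

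**The case against.** The strongest reply is that the independent t test may already be the link. With a single arm, responder subgroups are a natural source of independent groups, and the same paragraph specifies paired tests where it means pre-post change. A reader might therefore infer too much from saying that no analysis relating neurophysiology to response is planned. That stands: the text is ambiguous. What can be said is that no analysis is explicitly linked, and both readings of the t test need repair.

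A reader might also infer that the third objective cannot be delivered. The article does not support this. HRSD-24 and TMS-EMG/EEG are to be collected in the same patients, and nothing prevents relating them. The neurophysiological-change part of the objective, which is also the Introduction's third hypothesis, does have an analysis.

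A third tempting inference is that only baseline values can be predictors. The visit schedule is in an appendix that is not shown, and a change measured early in treatment, before the outcome, can properly be studied as a predictor. The narrower point holds: change over the same interval as the outcome is a correlate.

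It is also fair that this is an exploratory outcome of a pilot, that the Discussion claims only preliminary data and concedes the small sample, and that modelling detail is commonly left to an analysis plan. That lowers the weight of the point but does not remove it. The article does state its neurophysiology tests, down to tail and cortical site, and what it states does not match its own objective.

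**Conclusion.** The concern holds as a mismatch between stated objective and stated analysis. The permutation test addresses change only. The independent t test is either the wrong test for paired data or an undefined and weak responder comparison. Carried out as written, the plan gives no clearly stated result to support the deliverable on markers of response.

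The fault itself is one of specification and has no numerical size. The power and interval figures describe how little 25 patients can show. They rest on assumed effects (0.8 SD, correlations of 0.3 and 0.4), assumed splits, a 5% level and, unless stated otherwise, complete data on all 25. The protocol gives none of these except the 25. The point should be corrected but does not threaten the trial: the aim is exploratory and the remedy uses data already to be collected.

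**What to change.** In Statistical and Analytical Plans:

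1. State what the t test on TMS-evoked components compares. For pre-post change, use a paired comparison.
2. Add a pre-specified exploratory regression of week-4 HRSD-24, kept continuous, on one or two named TMS measures taken at baseline or early enough to precede the outcome, adjusted for baseline HRSD-24. Report slopes with 95% confidence intervals.
3. If change in a TMS measure over the same interval as the outcome is related to HRSD-24, label it a correlate.
4. If responder groups are kept for description, state the response definition.

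In the abstract's Conclusions, replace *determine* with *explore*, in line with the Objective and the Discussion.

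The cost is one added analysis, with no new data collection. Its intervals will be wide, and the claim about markers becomes more modest.

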**Methods:**

A sterile solution of racemic ketamine hydrochloride will be administered twice per week for 4 weeks (8 sessions) intranasally to patients with treatment-resistant depression who did not respond to or could not tolerate an acute course of electroconvulsive therapy. We will recruit 25 adults (24-65 years old) over the course of 2 years from an academic psychiatric hospital in Toronto, Canada.

**Results:**

This study has received ethics approval, and funding has been secured. The study is currently active.

**Conclusions:**

This is the first study to test repeated doses of intranasal rketamine in patients who have not responded to electroconvulsive therapy for depression. Results from this study will (1) inform the development of a larger adequately powered randomized controlled trial to test the efficacy of intranasal ketamine for depression and (2) determine potential neurophysiological markers of clinical response.

**Trial Registration:**

Clinical Trials.gov NCT05137938; http://clinicaltrials.gov/ct2/show/NCT05137938

**International Registered Report Identifier (IRRID):**

PRR1-10.2196/30163

## Introduction

Depressive disorders remain common, severe, and debilitating, with a lifetime prevalence estimated at 16.2% [1]. Research suggests that between 20% and 40% of patients with depression do not respond adequately to pharmacotherapies such as selective serotonin and serotonin–norepinephrine reuptake inhibitors, tricyclic antidepressants, or other psychotherapeutic interventions [2], and thus, are diagnosed with treatment-resistant depression [3]. Electroconvulsive therapy continues to be the gold standard therapeutic approach for treatment-resistant depression [3]. The Consortium for Research in Electroconvulsive Therapy [4] reports a 65% remission rate after 10 sessions that is consistent across the spectrum for bipolar and unipolar depression [5], with some previous studies also reporting remission rates as high as 70% to 90% [4,6]. However, despite these high efficacy rates, 10% to 30% of patients do not respond to electroconvulsive therapy, and these patients are left with very few treatment options [7].

Ketamine, a noncompetitive high-affinity *N*-methyl-D-aspartate (NMDA) receptor antagonist, has been shown to exert rapid and robust antidepressant effects in patients with treatment-resistant depression [8]. Studies have demonstrated that a single intravenous infusion of an NMDA antagonist resulted in significant decreases in depressive symptoms [9], making ketamine an attractive treatment option with the ability to simultaneously reduce neuronal activity in the limbic and subcortical regions while increasing activity in the prefrontal cortex [10], an area of core dysfunction reported in those with depression [10]. Numerous studies [11,12] have demonstrated that a subanesthetic dose of ketamine (0.5-0.8 mg/kg) over 40-minute intravenous infusion produces rapid antidepressant effects in patients with treatment-resistant depression. It has also been reported that the route of administration of ketamine can influence the clinical antidepressant effects of treatment owing to its extensive first-pass metabolism; specifically, the highest bioavailability of ketamine is achieved via intravenous infusion, while oral administration yields the lowest bioavailability [13]. Findings suggest that 70% of patients with treatment-resistant depression respond to 1 to 3 administrations of ketamine, and 30% to 60% of patients with treatment-resistant depression experience remission of their depressive symptoms. Research suggests that most responses occur if ketamine is administered in 6 or more sessions over a >2-week period [8,12].

Although intravenous ketamine has demonstrated rapid antidepressant effects, its delivery method remains challenging because it requires specialized expertise and equipment for administration [11]. Intranasal drug delivery, while preserving the rapid onset of therapeutic action, offers a route to the brain that bypasses problems associated with gastrointestinal absorption, first-pass metabolism, and the blood-brain barrier, and thus, minimizes the inconvenience and discomfort of parenteral administration [14]. Studies [15] indicate that intranasal rketamine has an absolute bioavailability of 50%, with a maximum plasma concentration achieved at approximately 20 minutes. This is consistent with other studies [13,15-17] in which the reported bioavailability of intranasal rketamine was demonstrated to be 45% to 50%. Converging evidence indicates that using intranasal ketamine with a dose range of 50-175 mg taken in intervals of 3 to 7 days can positively affect mood symptoms with a limited number of side effects [10]. Recently, esketamine (Spravato) received regulatory approval from the US Food and Drug Administration and Health Canada. However, it remains out of reach for most people with depression due to high costs and limited availability. To our knowledge, the clinical effects of intranasal rketamine have not yet been studied in a group of individuals with treatment-resistant depression who have not responded to electroconvulsive therapy.

Noninvasive brain stimulation neurophysiological tools, such as transcranial magnetic stimulation (TMS), offer an elegant opportunity to study mechanisms of human cortical physiology at the systemic level. The combination of TMS with a central nervous system pharmacological agent, such as ketamine, provides a platform to explore the neurophysiological impact of ketamine and allows neurophysiological biomarkers of treatment response to be identified. Until recently, only a few studies [16-18] have attempted to examine excitatory and inhibitory circuits by using a range of TMS protocols during infusion of incremental doses of ketamine, primarily using very low or single doses of ketamine in healthy volunteers. Currently, the research on predicting therapeutic response in those with mood disorders, measured by changes in cortical excitability, continues to be in very early stages and has not been systematically tested, making this proposal uniquely positioned among other neurophysiological studies [16,17,19] on ketamine and TMS. Our group has previously demonstrated impaired γ-aminobutyric acid inhibition from the motor cortex in patients with depression, a finding that was most pronounced in patients with treatment-resistant depression [18]. Additionally, Croarkin et al [20] demonstrated impaired NMDA receptor-mediated excitation in adolescent depression. The impact of ketamine on an excitatory or inhibitory cortical network will be assessed using neurophysiological tools such as TMS, specifically via short-interval cortical inhibition paradigms [21],

In this study, we aim to assess the safety and feasibility of intranasal rketamine in patients with unipolar depression who did not respond to the acute course of electroconvulsive therapy to inform a larger randomized controlled trial and examine potential neurophysiological biomarkers of response. TMS- electromyography (EMG) and electroencephalography (EEG) paradigms can be used to investigate the impact of ketamine on cortical activities via intracortical facilitation and short-interval cortical inhibition paradigms [19,22-26]. Based on accumulating evidence supporting the efficacy and tolerability of ketamine, we hypothesize that intranasal rketamine administered twice per week over 4 weeks will (1) result in improvement in depressive; (2) be safe and well tolerated in patients with treatment-resistant depression who could not tolerate or have not responded to electroconvulsive therapy; (3) result in neurophysiological changes. The results of this study will provide an important characterization of the neurophysiological effects of rketamine on cortical neurophysiology [19,22-26], which may serve as a ketamine biomarker and would be a crucial breakthrough in determining potential predictors of clinical response for depression.

## Methods

### Design

This is an open-label pilot study to assess the feasibility of conducting a randomized controlled trial to test the safety, tolerability, and efficacy of intranasal ketamine in patients with treatment-resistant depression who did not respond or were not able to tolerate a course of acute electroconvulsive therapy.

### Ethics Approval

This study has received Centre for Addiction and Mental Health (CAMH) research ethics board (095-2019) and Health Canada approval. For this pilot trial, all relevant adverse events and all serious adverse events will be reported if they meet applicable reporting requirements. All data monitoring, auditing, and harms reporting will be performed according to CAMH research ethics board and regulatory standards.

### Recruitment and Feasibility

#### Recruitment

Over a period 2 years, we intend to recruit 25 adults aged 24 to 65 years old diagnosed with treatment-resistant depression from one site (CAMH).

#### Participants

Patients will be assessed for eligibility based on inclusion and exclusion criteria.

#### Inclusion and Exclusion Criteria

Inclusion criteria are patients who (1) have a DSM-5 diagnosis of nonpsychotic major depressive disorder, confirmed by the Mini-International Neuropsychiatric Interview; (2) meet criteria for being nonresponsive to electroconvulsive therapy in the current episode (nonresponse is defined as lack of improvement in depressive symptoms after 8 acute sessions of electroconvulsive therapy, confirmed with the Hamilton Rating Scale for Depression (HRSD-24 score >14), and nontolerability is determined by a brain stimulation psychiatrist based on side effects, such as postictal confusion, significant cognitive impairment, severe worsening in anxiety preventing a patient from continuous treatment, or failure to secure intravenous access safely); (3) exhibit moderate to severe symptoms of depression (HRSD-24 score >14); (4) are capable of providing consent; (5) are outpatients; (6) are able to speak and understand English; and (7) are aged 24 to 65 years, inclusive.

Exclusion criteria are patients (1) with a history of a substance use disorder within the past month or lifetime history of ketamine substance use disorder, confirmed by the Mini-International Neuropsychiatric Interview; (2) with concomitant major unstable medical illness (eg, poorly controlled blood pressure; enlarged prostate; unresolved urinary related issues); (3)with a confirmed pregnancy or the intention to become pregnant and breastfeeding during the study (self-report), and female participants of reproductive age must be willing to use a medically acceptable method of birth control that includes highly effective (eg, approved hormonal contraceptives, intrauterine device, tubal ligation), double barrier (eg, male condom with a diaphragm, male condom with cervical cap) methods of contraception, or abstinence if that is the usual and preferred lifestyle of the participant; (4) with cardiac decompensation or heart failure; (5) with a DSM-5 diagnosis of any primary psychotic disorder, bipolar disorder, obsessive-compulsive disorder, or current posttraumatic stress disorder, confirmed by the Mini-International Neuropsychiatric Interview; (6) with a diagnosis of severe personality disorder, assessed during the initial consultation with a physician at the study site prior to study entry; (7) with any significant neurological disorder (eg, a space-occupying brain lesion, a history of stroke, a cerebral aneurysm, a seizure disorder, Parkinson disease, Huntington chorea, multiple sclerosis), assessed through medical history review during the initial consultation with a physician at the study site prior to study entry; (8) with a medical condition, taking medication, or with a laboratory abnormality that could cause a major depressive episode or significant cognitive impairment in the opinion of the investigator; (9) requiring a benzodiazepine with a dose equivalent to lorazepam 2 mg/day or higher; (10) on any anticonvulsant (eg, lamotrigine) or opioid medication due to the potential of these medications to limit the efficacy of ketamine; (11) with the inability to communicate in spoken and written English fluently enough to complete the required study assessments due to a language barrier or a noncorrectable clinically significant sensory impairment (ie, cannot hear or see well enough to complete clinical assessments); (12) with any cognitive or physical impairment which may potentially interfere with intranasal ketamine administration or the patient’s ability to stay in the same place for a 2-hour monitoring supervision, assessed through medical history review during the initial consultation with a physician at the at the study site prior to study entry; (13) with any intracranial implants (eg, aneurysm clips, shunts, cochlear implants) or any other metal object within or near the head, excluding the mouth, that cannot be safely removed given that we will be using TMS-EMG/EEG; (14) with the inability to secure escort to accompany them back home after ketamine sessions; or (15) with any known allergy to ketamine or any component or ingredient of the ketamine preparation.
